#### Further secondary outcomes

*Treatment adherence* will be measured using an in-house-developed, short, 30-item Treatment Adherence Questionnaire. PIP therapists are asked to evaluate after each session the methods and interventions applied

*Health care and social services utilization and costs*. To estimate the economic consequences on the health care service usage in Germany, a cost analysis will be carried out in both groups by using a self-developed resource consumption questionnaire. Questions about the utilization of health and social care and demand on early intervention services are assessed. The questionnaire will be applied at T0 and T2. These data are used for calculation of health care costs. Therefore, these resources will be monetarily assessed by using standardized unit costs from a societal perspective, which will be calculated based on regularly published sources.

### Samples size calculations and statistical analyses

A power analysis [G*Power] based on a reported moderate to large effect size of Cohen’s *d* = 0.64 for a difference in maternal sensitivity after 6 weeks of intervention between the intervention group and the CAU group [19] and two-tailed testing with a significance level of *α* = 5% using an analysis of covariance (ANCOVA) (with maternal sensitivity at T1 as the dependent variable and maternal sensitivity at T0 as a covariate) resulted in a required sample size of *n* = 70 (per group) to detect an effect with a power of 95%. With an assumed drop-out rate of about 20% [1] the sample size calculates to *n* = 90 per group (total sample size *n* = 180 mother-child-dyads).

The statistical analysis will be carried out at the end of the last follow-up assessment and all analyses will be conducted in accordance *with intention-to-treat (ITT)* principles and will be including all randomized mother-child-dyads in the study. The *Full Analysis Set (FAS) will be used for all analyses (unless otherwise stated),* it will include all randomized mother-child-dyads. Data will be analyzed according to randomization irrespectively of the treatment received. Data from mother-child-dyads that have withdrawn from the study will be included in the FAS up to the date of their termination. The *Per-Protocol (PP) population* will comprise a subset of the FAS. It will consist of mother-child-dyads who will have received treatment according to the randomization, will have adequate therapy adherence, and no major protocol violations. Major protocol violations will be considered as not meeting all inclusion criteria, a change of treatment group or as the PIP intervention that has not been carried out properly according to the treatment manual. The *safety population* will include mother-child-dyads who have participated in at least one intervention session. Participants in the safety population will be analyzed according to the treatment actually received.

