### Intervention

*Focused Parent-Infant-Psychotherapy* is a psychotherapeutic intervention in which mother-child-dyads are treated together. Individual sessions could also be held together with the father. PIP aims at fostering the parent-infant-relationship by supporting the parents’ ability to understand and mentalize the child’s affective states. It aims at promoting parental self-reflection and sensitivity to support the building and maintaining of parent-infant-relationships. PIP interventions are exclusively delivered by trained and supervised psychotherapists who are additionally certified in the PIP method. The manualized PIP ([name], [name], [name]: SKKIPPI-Studymanual for Parent-Infant-Toddler-Psychotherapy (PIP), unpublished) is a focused psychodynamic intervention with 12 succeeding sessions of approx. 50 min in 6 weeks (two sessions per week). The aims of PIP are clarification of problems, affect regulation, self-reflection, a change of perspective and the activation of the participants’ interpersonal resources. The intervention includes a mentalization-based approach, and works with reframing, an appropriate confrontation within a supportive framework, psychoeducation, the development of action strategies, and video-feedback. To enhance manual adherence, all study therapists will be additionally trained in the manual before the start of the treatment.

The inpatient treatment is characterized by interventions in adult psychiatric departments with MBUs or day hospitals. In inpatient settings, PIP will be provided in addition to standard therapeutic care. In outpatient settings PIP will be provided in the patients’ home environment or in psychiatric outpatient departments.

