### Control

Participants in the CAU group will benefit from the standard (social) pedagogical and therapeutic care provided by the German health system over the intervention period of 6 weeks. Due to ethical considerations, no “waiting-list” group will be implemented. CAU, therefore, will resample a heterogeneous class of standard interventions. As a result, more intense and therapeutic care might be provided for mother-child-dyads in the inpatient settings compared to standard care in the outpatient setting. CAU in the inpatient setting could include counseling, body or occupational therapy and other psychiatric-therapeutic interventions for the participant. The frequency of these interventions will be generally lower than PIP treatment. CAU in outpatient setting could be other therapeutic interventions or (social) pedagogical care such as developmental psychological counseling or physiotherapy. Because this might result in heterogeneities in the number and intensity of CAU, all individual interventions will be documented.

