### Ethical considerations and limitations

Data will be assessed, processed and stored according to the data protection laws and the local data protection protocol. The research project will be carried out in compliance with the study protocol and the Declaration of Helsinki (1996 version, Somerset West). All researchers and participants in the study are obliged to follow the rules of Good Clinical Practice (ICH-GCP). Participants will only be enrolled in the study after giving inform consent. The study is designed as an open RCT with blinded endpoint assessment and blinded analysis. Still, participants will be aware of their treatment group allocation.

This trial compares a psychotherapeutic intervention with available CAU interventions. The CAU interventions will be heterogeneous and administered under very diverse conditions. Therefore, it will be difficult to document which component of CAU is most effective. Moreover, there will be differences in CAU depending on the setting (inpatient vs. outpatient). Due to ethical concerns participants will not be randomly allocated to a setting. Thus, more severe cases will be evident in the inpatient setting, lowering the representativeness of the results. At the same time the CAU routine intervention will be more intense in inpatient departments, i.e., CAU in inpatient settings will likely include other (psycho-)therapeutic interventions. Furthermore, ethical consideration precluded the inclusion of a waiting-list group. This very same concerns will also lead to the fact that all mother-child-dyads allocated to CAU will be offered an intervention or CAU. Thus, the standard in the CAU will likely be higher than in the overall population in Germany which will bias generalizability of the results. In order to minimize these effects and to incorporate these limitations in the analyses, all interventions in all conditions will be documented.

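### The safety population requires at least one intervention session, but usual care has no defined sessions, so the control side is either empty or selected by service uptake after randomisation

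*Protocol article*

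**What the plan says.** All three analysis sets are defined in the protocol article under *Samples size calculations and statistical analyses*. For the full analysis set, "it will include all randomized mother-child-dyads". The safety population is narrower: it "will include mother-child-dyads who have participated in at least one intervention session". The next sentence fixes the grouping: "Participants in the safety population will be analyzed according to the treatment actually received".

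The two arms are described very differently. *Intervention* sets PIP out as twelve sessions of about 50 minutes, two a week for six weeks. *Control* gives no such schedule: "CAU, therefore, will resample a heterogeneous class of standard interventions". For outpatients, "CAU in outpatient setting could be other therapeutic interventions or (social) pedagogical care". The same section expects variation in how much care is received: "this might result in heterogeneities in the number and intensity of CAU, all individual interventions will be documented". *Ethical considerations and limitations* describes control care as an offer: "all mother-child-dyads allocated to CAU will be offered an intervention or CAU".

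**The concern.** The entry rule and the grouping rule fit together only if every control dyad has something that counts as an intervention session. Nothing in the protocol secures that. The phrase is not defined for CAU, and wherever else the article speaks of sessions (*Abstract*, *Intervention*, *Further secondary outcomes*, *Methods to minimize bias*, *Ethical considerations and limitations*) it means PIP sessions.

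At stake is the comparator for any safety summary. The participants are mothers with diagnosed mental disorders. An event in a CAU mother who took up no service would be documented but would fall outside the set on which safety is to be reported. A control group formed by who happened to use a service is no longer the randomised control group.

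**Working it through.** **1. Size of the control arm.** Inputs from *Samples size calculations and statistical analyses*: 70 dyads per group and about 20% drop-out. 70 / (1 − 0.20) = 87.5, rounded up to 88. The plan states 90, which agrees to within two dyads. The planned CAU arm is therefore 90.

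**2. Reading A: an intervention session is a PIP session.** Every member of the safety set has then received PIP. Grouped by treatment received, every member is analysed as PIP, and the CAU group contains 0 of 90. A CAU-allocated dyad that did receive PIP would enter, but as PIP. The as-treated sentence then has nothing to separate.

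**3. Reading B: any documented PIP or CAU contact counts.** Let u be the share of CAU dyads with no contact. The control side is 90 × (1 − u) and the loss is 90 × u. The protocol gives no value for u, so the range below is an assumption. The last column is the one-sided 95% upper limit for an event risk when no events are seen among m dyads, 1 − 0.05^(1/m).

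| u (assumed) | CAU dyads lost | CAU dyads left (m) | Upper limit with zero events |
|---|---|---|---|
| 0% | 0 | 90 | 3.3% |
| 5% | 4.5 | about 86 | 3.4% |
| 10% | 9 | 81 | 3.6% |
| 20% | 18 | 72 | 4.1% |
| 30% | 27 | 63 | 4.6% |
| 50% | 45 | 45 | 6.4% |

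If the risk of a severe event were 2% (also an assumption; the protocol gives no rate), the chance of seeing at least one among controls, 1 − 0.98^m, would be 84% with 90 dyads, 77% with 72 and 60% with 45. The loss of precision is modest at small u. The more basic problem is that the remaining dyads are selected by what they did after randomisation.

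**4. The same phrase also decides the arm.** *Intervention* says that inpatient PIP is added to standard care. Take an inpatient dyad allocated to PIP that attends no PIP session. Under reading A it is excluded. Under reading B it enters through its standard care and, analysed as treated, would count as CAU. One undefined phrase therefore settles both membership and group.

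**The case against.** The strongest reply is that reading A cannot be intended. Analysing by treatment received presupposes a CAU group, and *Control* calls the components of CAU interventions and has them all documented. The sensible reading is then at least one PIP or CAU contact, and requiring one treatment contact is a conventional safety-set rule. This largely stands: a reader might infer that all 90 CAU dyads will be excluded, but the document as a whole does not support that as the plan's intention. It shows only that the literal wording leads there.

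On reading B, the word *could* in the outpatient description lists kinds of care; it does not say that care may be absent. All CAU dyads are to be offered something, and the protocol expects their standard of care to exceed that of the general population. So u may be small or zero. That stands too, but an offer is not uptake, and no sentence admits a CAU dyad without contact.

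A reader might also infer that the rule makes PIP look less safe. That requires CAU non-users to have more events than users. They could equally be milder cases, and excluded dyads leave both numerator and denominator. The direction is not established.

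Nor are events hidden from oversight. *Monitoring and trial management* has severe events reported to the ethics committees with the advisory board consulted, and *Ethical considerations and limitations* says that severe events are documented and enter the statistical analyses. The article specifies no between-arm test of adverse events, and that detail may sit in a fuller document. But the population rule is stated here, so it is not something merely left for later.

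**Conclusion.** The point holds as a defect in a stated definition. As written, the safety population either has no control group, which contradicts the sentence that follows it, or has a control group selected on service uptake after randomisation.

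The size cannot be computed from the protocol. It is 90 × u on the broader reading, with u unknown and possibly zero. Any percentage loss quoted for the CAU arm rests on an assumed u, and no particular figure should be presented as the plan's own.

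Only the safety set is affected. The primary analysis, and every other analysis not stated otherwise, uses the full analysis set with all randomised dyads. This is a change that should be made because it is nearly free, not because an efficacy conclusion is at risk.

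**What to change.** Drop the session requirement for the control arm and restate the safety population along these lines:

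- The set includes all randomised dyads.
- Dyads with at least one PIP session are analysed as PIP.
- CAU-allocated dyads with no PIP session are analysed as CAU, whether or not they used any service.
- Events are counted over the same period from randomisation in both groups.

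PIP-allocated dyads that attended no PIP session need an explicit rule. Moving them into CAU without comment would add a selected group to the comparator. Report them separately, or add a summary by randomised arm to show that their placement does not matter.

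The change takes a few sentences in the analysis-set definitions and should be made before unblinding. No new data are needed, since individual interventions and severe events are already to be documented. The cost is a small amount of extra tabulation.

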#### Primary analysis of the primary outcome

The evaluation of the primary outcome (EAS, maternal sensitivity at T1) will be performed by a covariance analysis (ANCOVA) with the independent variable treatment (PIP vs. CAU), adjusted for maternal sensitivity at baseline (T0) and treatment setting as stratification variable based on the FAS population. Adjusted mean values of treatment groups with 95% confidence intervals and *p* value (two-sided) for group comparisons will be presented.

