### Trial design

The study will be designed as a two-arm, open, multi-center RCT with parallel groups and blinded endpoint assessment (PROBE design; prospective, randomized, open, blinded endpoint) with 6 weeks of intervention.

Depending on the severity of the psychopathological symptoms and in agreement with the participants’ preferences, the decision for a particular treatment setting (inpatient or outpatient) will be made before randomization. After assignment to treatment setting, participants will be randomly allocated to either the PIP intervention group or the CAU control group. A biometrician will independently carry out a 1:1 block randomization with variable block length and stratification by setting (inpatient or outpatient) and study center. Treatment allocation is masked to the assigning personnel and there will be no special criteria for discontinuing or modifying the allocated intervention. Data of mothers and children will be assessed at three measurement points (see Fig. 1): at baseline after randomization and immediately before the intervention (T0), after the intervention at 6 weeks (T1) and at 12-month follow-ups (T2). Study centers are located in the German cities Berlin and Flensburg. At the time of writing additional effort is being made for a study center in Hamburg.

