#### Secondary analyses of the primary outcome

The primary analysis will be repeated as described with the PP population. In addition, the effect of treatment setting on the efficacy of PIP will be investigated by means of a moderator analysis. Moderators show their effect in the interaction with treatment group. Thus, the model will include all variables as described for the primary analysis with the addition of the treatment*setting interaction. Additional moderator analyses regarding the effectiveness of PIP including maternal attachment style and reflective functioning (AAI) as moderators will be calculated. A sensitivity analysis of the primary outcome will be computed using multiple-imputation methods and the PP population adjusted for maternal sensitivity at baseline and treatment setting as stratification variable. In a further sensitivity analysis of the primary outcome, a hierarchical regression model will be calculated which, in addition to the adjustment for the baseline values and the treatment setting, will include the therapists who performed the intervention in the model. Both sensitivity analyses will be repeated using also study center as stratification variable.

Linear ,mixed models for longitudinal data will be used to examine the change of the primary outcome across all measurement time-points for the treatment groups. The model will include predictors for treatment group and time as fixed effects as well as the treatment group × time interaction, baseline maternal sensitivity as covariate, treatment setting as stratification variable, and subjects as random effects. The therapists and further predictors will be added to the model when indicated by goodness-of-fit model comparisons (based on Akaike Information Criterion (AIC) values). All secondary analyses of the primary and secondary outcomes are considered exploratory.

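### Randomisation is stratified by setting and study centre, but the primary ANCOVA adjusts for setting alone; if centre is prognostic after T0 and setting, the test is slightly conservative

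*Protocol article*

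**What the plan says.** - **Allocation.** Under Trial design, a biometrician carries out a "1:1 block randomization with variable block length and stratification by setting (inpatient or outpatient) and study center". Two centres are named ("Study centers are located in the German cities Berlin and Flensburg"), and a third in Hamburg is being sought.
- **Primary model.** Under Primary analysis of the primary outcome, the ANCOVA compares PIP with CAU, "adjusted for maternal sensitivity at baseline (T0) and treatment setting as stratification variable based on the FAS population". No centre term is listed, and no reason is given for leaving it out.
- **Where centre does appear.** Under Secondary analyses of the primary outcome, two sensitivity analyses are described: one with multiple imputation and the per-protocol population, and one hierarchical model that includes therapists. Then: "Both sensitivity analyses will be repeated using also study center as stratification variable". The same section adds: "All secondary analyses of the primary and secondary outcomes are considered exploratory".
- **Reach.** Under Analyses of the secondary outcomes, the secondary endpoints follow the primary outcome's strategy, so the covariate list carries over to them.

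**The concern.** Permuted blocks within centre keep the arms nearly balanced in each centre. Differences between centres therefore hardly contribute to the sampling variation of the treatment contrast. An ANCOVA without centre does not use this: it leaves any between-centre variance in the residual and computes the standard error as if that variance still affected the contrast. The estimate is sound, but the standard error attached to it can be too large.

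At stake is some precision in the confirmatory interval and some power, both of which the randomisation has already provided. The repeats with centre do not recover them. They are exploratory, they use other models or populations, and they do not include the primary ANCOVA itself. This is also not a detail left open for the analysis plan, because the article names the covariates of its confirmatory model and the list omits one of its two stratification factors.

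**Working it through.** **Inputs from the protocol article**
- Stratification factors: setting and study centre, 1:1 blocks of variable length (Trial design).
- Primary covariates: T0 sensitivity and setting (Primary analysis of the primary outcome).
- Design effect d = 0.64, two-sided α = 5%, power 95%, 70 per group, about 20% dropout, 180 randomised (Samples size calculations and statistical analyses).
- Evaluable dyads: 180 × (1 − 0.20) = 144, or 72 per group.

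**Assumption.** Let ρ be the share of the residual variance, after T0 and setting, that is due to centre. The article does not give it. The values used are 0%, 5% and 10%, with 20% as a stress case in the simulation.

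**The plan's own figure.** For d = 0.64, two-sided 5% and 95% power, a two-group comparison needs 64 per group (normal approximation) or 65 (t/ANCOVA), against the stated 70. Power at 70 per group is 96.4%, so the stated number errs on the safe side. The dropout step gives 70/0.80 = 87.5, or 88, against the stated 90. Neither difference affects the present point.

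**Closed form** (residual SD 1 including the centre part, near-perfect balance within strata)
- Reported SE without centre: SE₀ = 2/√144 = 0.1667.
- True sampling SD of the estimate: SE₀ × √(1 − ρ).
- SE inflation: 1/√(1 − ρ).
- True type I error: 2 × [1 − Φ(1.96/√(1 − ρ))].
- Power without centre: Φ((δ − 1.96 SE₀)/(SE₀√(1 − ρ))).
- Power with centre: Φ(δ/(SE₀√(1 − ρ)) − 1.96).

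| ρ | true SD | SE too large by | true type I | power at 0.64, without / with centre | power at 0.5, without / with centre |
|---|---|---|---|---|---|
| 0% | 0.1667 | 0% | 5.0% | 97.0% / 97.0% | 85.1% / 85.1% |
| 5% | 0.1624 | 2.6% | 4.4% | 97.3% / 97.6% | 85.7% / 86.8% |
| 10% | 0.1581 | 5.4% | 3.9% | 97.6% / 98.2% | 86.4% / 88.5% |

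The power lost is 0.3 and 0.5 points at d = 0.64, and 1.1 and 2.2 points at 0.5 SD. Here δ is in units of the residual SD. The 0.5 SD column is illustrative and is not a figure from the plan.

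**Simulation check.** The set-up was 144 dyads, permuted blocks of 2, 4 or 6 within setting by centre, and two equal centres, with 8,000 null runs and 4,000 power runs per scenario. The Monte Carlo standard error of the type I rates is √(0.05 × 0.95/8000) = 0.24 points.

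| ρ | mean SE, without / with centre | sampling SD, without / with | type I, without / with | power at 0.5 SD, without / with |
|---|---|---|---|---|
| 0% | 0.167 / 0.167 | 0.166 / 0.166 | 4.6% / 4.6% | 84.5% / 84.3% |
| 5% | 0.167 / 0.163 | 0.164 / 0.164 | 4.5% / 5.1% | 85.3% / 86.5% |
| 10% | 0.167 / 0.158 | 0.161 / 0.161 | 4.1% / 5.2% | 86.3% / 89.0% |
| 20% | 0.167 / 0.149 | 0.150 / 0.149 | 2.9% / 4.9% | 86.9% / 91.3% |

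Three centres in proportions 50/30/20 give the same pattern: type I error of 4.3%, 3.9% and 2.7% without centre at ρ = 5%, 10% and 20%, against 4.8%, 5.1% and 4.7% with it. In every scenario the estimate varies almost equally under both models; only the reported SE differs. At ρ = 0 the centre term costs nothing measurable.

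**The case against.** The strongest case against raising this has four parts.

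1. **The harm is conditional.** T0 sensitivity and setting are already in the model, and setting is chosen partly by symptom severity. Centre differences in baseline sensitivity, and the part of case mix that setting carries, are therefore largely absorbed. Only what remains matters. With two or three centres, a common manual, trained and supervised therapists and blinded coders, there is no reason to presume that the remainder is large. This stands, and it is why the table starts at 0%.
2. **The direction is safe.** The estimate is unbiased and the type I error does not exceed 5%, so a significant result under the planned model would hold. This stands.
3. **The loss is small at the planned effect.** At d = 0.64 it is about half a point at most for ρ up to 10%, and power stays above the 95% target. This stands.
4. **Centre is not ignored.** The sensitivity repeats will show something of its influence. This stands only in part: they are exploratory, and none of them is the primary ANCOVA with centre added.

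A reader might also infer that the omission wastes ρ × 144, or about 7 to 14 evaluable dyads. That overstates it. The estimate loses almost no information; only its reported SE is inflated. At ρ = 10% and 0.5 SD, omitting centre costs 2.2 points (88.5% to 86.4%, from unrounded values), whereas removing 14 dyads (144 to 130) from the analysis with centre would cost 3.4 points (88.5% to 85.2%, likewise).

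**Conclusion.** The mismatch is certain from the text: two stratification factors, one of them in the confirmatory model. Its consequence is conditional and modest. If centre explains 5–10% of the variance left after T0 and setting, the primary SE is 2.6–5.4% too large and the nominal 5% test runs at about 4.4–3.9%. The power cost is 0.3–0.5 points at the planned effect and 1–2 points at 0.5 SD. If centre explains nothing, the planned analysis is correct as written.

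A reader might infer that the primary interval is definitely too wide, or that the primary result would be invalid. The article supports neither: it gives no centre variance, and any error is on the conservative side.

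The size rests on the assumed ρ, on 144 evaluable dyads, and on the within-centre balance surviving dropout. The point is worth acting on because the remedy is nearly free, not because the harm is large.

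**What to change.** Before unblinding, define the primary model as EAS sensitivity at T1 = treatment + T0 sensitivity + setting + study centre, with centre as a fixed effect. State in advance how a very small centre will be handled, which matters if Hamburg joins late. Use the same covariates for the secondary outcomes that follow the primary strategy. Keep the ANCOVA without centre as a sensitivity analysis.

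The cost is one line of wording and 1 degree of freedom for two centres or 2 for three, out of about 140. No new data are needed and the sample size does not change. The article unblinds outcome data only after the last participant has finished, so the change can be made cleanly before then.
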